#### Sample size of community health nurses

To evaluate the projected 4,100 women over a year with approximately 220 working days, we estimate that a total of 19 examinations will be performed daily across the three selected PHCs in the intervention LGA. Three CHNs per facility (nine in total) will be trained to take focused breast history, perform the examinations (iBE and CBE), triage patients for imaging, and navigate patients through the referral pathway.

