#### Screening and diagnostic evaluation schedule in the intervention arm

In the intervention arm, consecutive consenting asymptomatic (40–70 years) and symptomatic (30–70 years) women will undergo screening and diagnostic evaluations respectively. Asymptomatic women (age 40–70 years) presenting for screening at designated PHCs will be evaluated by trained CHNs. Evaluation will entail a focused breast history, CBE, and iBE. Women with positive findings on CBE or iBE will be scheduled for another visit to have breast imaging and if indicated a breast biopsy. Women with negative findings on CBE and iBE will be scheduled for a similar repeat annual evaluation. Women will, however, be told to return at any time if any abnormality is noticed before their scheduled visit. Every woman who is screened will be given a breast health card (pink card) containing her name, contact information, a summary of findings on evaluation, and the date of the next examination. A duplicate copy of the breast card will be kept at the health centre for reference and follow-up. In addition to the breast health card, a detailed record of CBE and iBE findings for each patient will be kept by the PHC Nurse.

Symptomatic women (age 30–70 years) without an obvious lesion will be evaluated like the asymptomatic population, with focused breast history, CBE, and iBE. Those with positive findings will progress to imaging while those with negative findings will be scheduled for repeat evaluation on a short-term basis (one month). If symptoms persist at the time of the next evaluation, they will progress to imaging regardless of CBE and iBE findings.

Symptomatic women (age 30–70 years) with obvious breast lesion(s) will undergo focused breast history and CBE examination and will be scheduled to have imaging evaluation and breast biopsy if indicated (Fig 3).

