#### Program evaluation and outcome measures

The study timeframe is 2 years; however, a descriptive analysis will be carried out at 1.5 years to evaluate for the retention of study participants. A review will also be done at the end of year one to evaluate the progress of the research. Breast screening practices of the entire LGA will be re-assessed at the end of the first year in both the intervention and control LGAs. This will be compared with the baseline data already obtained before the commencement of the study to determine the impact of the intervention on breast cancer awareness and screening practices.

A full evaluation will be done at the end of 2 years. The following outcomes (Fig 4) have been defined a priori and will be used as metrics to assess the impact of the program.

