Participation rate: This will be determined by calculating the percentage of women screened/evaluated of the total number of eligible women based on census data. A participation rate of 70% will be considered satisfactory in the intervention arm. The number of screened/evaluated women in the intervention and control arms will also be compared.Cancer detection rate (CDR): This refers to the number of histopathologically diagnosed cases of breast cancer per 1,000 evaluated populations in both screening and diagnostic groups. This will be compared between the control and intervention arms.Timeline from presentation to treatment: The time interval between presentation for breast evaluation and treatment in OAUTHC of the cases in the two arms will be compared.Retention rate: The retention rate refers to the number of women who return for repeat annual screening of the total initial number of women initially screened in the first year. A repeat screening within a year and a half will be considered acceptable for this two-year study. To ensure all accrued participants get their second screen, we will follow them up beyond the initial study period as needed.Abnormal call rate: This is defined as the number of women with abnormalities detected on iBE and/or CBE requiring further evaluation either by imaging with or without biopsy out of the total number of asymptomatic and symptomatic without an obvious lesion participating in the study. There are 2 groups of participants (diagnostic and screening) in each of the 2 arms (intervention and control). The screening group constitutes the asymptomatic participants while the diagnostic group constitutes the symptomatic participants. The interventions in this study include enhanced CBE (CBE + iBE), community-based diagnostic evaluation (with portable ultrasound and mobile mammography), and biopsy (if warranted). To evaluate which of CBE and enhanced CBE was of greatest value, another layer of analysis will be provided to address this question by comparing the concordance of the two with imaging which is the gold standard. This study also provides an additional opportunity to evaluate the iBE device.

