A descriptive analysis of the data will be done at 1.5 years for the retention rate and abnormal call rate to inform our decision for future investigations. The rate of late-stage diagnosis will be estimated on a yearly basis. However, no stopping rules will be employed. This estimation will purely serve the purpose of detecting any difference in the annual trends of the stage of diagnosis over time between the intervention and control arms.

The initial findings for the subset of women who undergo a second round of screening will be examined to identify the stage of presentation in this group of women if diagnosed during the second round. Given in our setting ~80% of patients with breast cancer present in stages 3 and 4, we expect to see a trend toward earlier stage of presentation (stages 0, 1 and 2) in women undergoing repeat breast evaluation.

The 2-year study period is enough to generate adequate data to measure the participation rate and difference in stage at diagnosis between the study arms, as elaborated in the sample size calculation of the cancer cases. In addition, this study will provide a groundwork for exploring the difference in CDR between the 2 modalities (CBE and enhanced CBE) and the time to treatment, generating data to guide future studies in our population.

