Feasibility and sustainability were central in the discussion during the design of this study. The investigators anticipate logistic constraints with the recruitment of the expected number of study participants by the recruiters who are CHNs in this study. To avoid overburdening the recruiting CHNs who perform many roles and responsibilities in the PHCs, the investigators have an understanding with the officer-in-charge (OIC) to exempt the recruiting CHNs from other responsibilities in the PHCs during the study period, which is a pragmatic way of ensuring efficient performance by the CHNs. The model proposed in this study is sustainable because of the vertical approach employed. Utilization of existing health facilities and personnel do not require significant financial and human resources commitment from the government. The government can then leverage its existing funding streams to provide the intervention package (both screening and diagnostic equipment) at a subsidized rate that will be affordable to the people.

Initially, recruitment for this study was slower than expected due to COVID-19 disruptions; however, there has been a progressive surge in the number of cases over time. This research may be challenged by the problem of contamination in the intervention and control arms. Patients particularly the symptomatic women who live outside the two selected LGAs may cross from their LGA and present in the study sites when they get informed of this research by people around them or through the ongoing radio adverts. This will be mitigated by carefully matching the residential addresses against the LGAs. This will be done by the RSAs immediately after the patients present in OAUTHC during navigation. To avoid contamination by women earlier confirmed to have breast cancer in OAUTHC, the RSAs will carefully probe into previous clinic visits by the patients in OAUTHC.

It is anticipated that this study will provide vital data to support wider breast cancer screening efforts in Nigeria through a partnership with the Ministry of Health. The results of this study could provide a breast cancer screening model for other resource-limited countries with similar population dynamics.

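### The 1.5-year retention rate counts women not yet due for their annual repeat as not retained, so it is biased downward, by an amount that depends on the accrual pattern

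*Protocol article*

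**What the plan says.** The retention entry under Secondary outcome measures (Protocol article, Program evaluation and outcome measures) fixes the rate as "the number of women who return for repeat annual screening of the total initial number of women initially screened in the first year". The denominator is every woman screened in year one. The same entry sets a tolerance for late returns: "A repeat screening within a year and a half will be considered acceptable for this two-year study". It adds that follow-up will run past the initial study period where this is needed for the second screen.

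The repeat interval comes from the screening schedule for the intervention arm: "Women with negative findings on CBE and iBE will be scheduled for a similar repeat annual evaluation".

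The timing appears twice. Program evaluation and outcome measures opens with "The study timeframe is 2 years; however, a descriptive analysis will be carried out at 1.5 years to evaluate for the retention of study participants", and the text after the outcome list says "A descriptive analysis of the data will be done at 1.5 years for the retention rate". The abnormal call rate is looked at alongside it, and the stated purpose is a decision about future investigations. Statistical analyses reports the retention rate as a simple proportion with an exact 95% confidence interval. Nothing in the article limits the denominator to women whose repeat has fallen due.

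**The concern.** The definition uses a full year of first screens, and the repeat comes 12 months after each of them. The last of these repeats is due at month 24, but the analysis is at month 18. Women first screened in months 6 to 12 are in the denominator and, if they keep to schedule, cannot yet be in the numerator. The 1.5-year figure therefore mixes two things: how many women come back, and how early in the year they were first screened. A reader who takes it at face value would think the programme loses more women than it does. Judging retention is a stated purpose of this look, and the result is meant to guide later work.

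**Working it through.** **Inputs from the article.** Denominator: all women first screened in months 0 to 12. Repeat due 12 months after the first screen. Return accepted up to 18 months, read as time since the woman's own first screen. Analysis at month 18 of a 24-month study. The document states no expected retention rate, so the 70% below is illustrative.

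**Planned accrual, reproduced first.** Sample size of community health nurses says "To evaluate the projected 4,100 women over a year with approximately 220 working days, we estimate that a total of 19 examinations will be performed"; the rate is per day. 4,100 / 220 = 18.6, rounded up to 19. This is a flat rate, that is, even accrual.

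**Share due at month 18.** A woman first screened at month u is due at u + 12, so she is due by month 18 only if u ≤ 6.
- Even accrual: 6/12 = 50%.
- Linearly rising accrual (assumed shape): (6/12)² = 25%.
- Linearly falling accrual (assumed shape): 1 − (1 − 6/12)² = 75%.

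**Observed rate as a fraction of true retention at month 18.** This is P(u + d ≤ 18), where d is the delay from first to repeat screen among women who do return.

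| Accrual | All return at 12 months | Returns even over 12–15 months | Returns even over 12–18 months |
|---|---|---|---|
| Even | 0.50 | 0.375 | 0.25 |
| Linear rise | 0.25 | 0.146 | 0.083 |
| Linear fall | 0.75 | 0.604 | 0.417 |

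For the even row, the mean of (6 − e)/12 over the delay e beyond 12 months gives (6 − 1.5)/12 = 0.375 and (6 − 3)/12 = 0.25.

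**Example.** True retention of 70% under even accrual shows as 0.70 × 0.50 = 35% if every return is on time, and as 0.70 × 0.25 = 17.5% if returns spread over 12 to 18 months.

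**The interval gives no warning.** The article reports 791 first-year patients in the intervention arm. For an observed 35%, the normal approximation gives 1.96 × √(0.35 × 0.65/791) = 3.3 percentage points either side, far from 70%. (The 791 include symptomatic women, so this is only an illustration.)

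**Later data cuts.** Windows for year-one women close between months 18 and 30. Under even accrual, all women are due by month 24, but only half of the windows have closed. With returns spread over 12 to 18 months, the observed fraction is (12 − 3)/12 = 0.75 at month 24 and 1.00 at month 30.

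**The case against.** The best case for the plan has five parts.

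- *It is only a descriptive look.* This is true and limits the weight. Retention is one of several secondary outcomes, it has no numeric target, no stopping rule depends on it, and the full evaluation comes at 2 years. The look is still meant to inform a decision, so a figure biased by construction is a defect.
- *Follow-up is extended.* This stands for the final rate. It cannot change a figure computed at month 18.
- *Accrual may be front-loaded.* Radio and television promotion is heaviest in the two weeks before launch and drops to weekly afterwards. Against this, the Discussion reports slow early recruitment and then says "there has been a progressive surge in the number of cases over time". That surge may mean recruits or cancer cases, and no monthly counts are given. The size of the bias is therefore uncertain. Its direction is not: front-loading shrinks the bias without removing it.
- *The interim denominator may be settled elsewhere.* A condensed article may leave data-cut details to the full plan. Here, however, the article states the denominator itself and gives no other for the 1.5-year look. The time point is set against the 2-year timeframe, so study time is the natural reading. If the year and a half allowed for a repeat also meant study time, women screened after month 6 would have to return before their repeat was due, and the rate would still be too low.
- *Multiple imputation.* The article offers it for data missing through loss to follow-up. Women not yet due are not lost, and the definition simply counts them as non-returners.

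**Conclusion.** The point holds as a downward bias in the 1.5-year retention rate. Under the even accrual that the planned daily rate implies, about half of the denominator is due, so the observed rate is at most about half of the true rate. It is a quarter of the true rate if returns spread evenly over 12 to 18 months. With back-loaded accrual the bias is larger, and with front-loaded accrual smaller. These ceilings assume that women do not return before 12 months; a few early returns would raise them slightly.

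A reader might infer three stronger things that the document does not support:

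- That the rate will understate retention by half or more whatever happens. This needs even or back-loaded accrual, and actual monthly accrual is not reported.
- That the figure reflects only how early women enrolled. It is a mixture of enrolment timing and true return.
- That the final retention rate is also wrong. The extended follow-up can protect it, provided it is computed after the windows have closed.

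Severity is minor to moderate: a named secondary outcome and a stated purpose of a planned look are affected, but the primary outcome and the trial's main comparison are not.

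**What to change.** Define retention per woman as a repeat screen within 18 months of her own first screen. At 1.5 years, and at 2 years while windows remain open, do one of the following:

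- restrict the denominator to women whose 12-month repeat is already due, and label the result as returned so far; or
- report cumulative return by time since first screen (Kaplan-Meier type), with women censored at the data cut.

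The first option removes the bias only for on-time returns. If returns spread evenly over 12 to 18 months, 0.25/0.50 = half of the eventual returners among women due have come back by month 18. The second option handles late returns, but it is well supported only for the earlier part of the window: under even accrual, 3/12 = 25% of women have been observed for 15 months at that cut and almost none for 18. Give the final rate once every 18-month window has closed, at month 30 for the last year-one women.

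The cost is one definition and some precision. Under even accrual the due-only denominator is about 2,050 of the planned 4,100, or about 396 of the 791 reported. At 70% retention the half-width goes from 1.96 × √(0.70 × 0.30/791) = 3.2 to 1.96 × √(0.70 × 0.30/396) = 4.5 percentage points. First and repeat screen dates are needed for each woman. The article does not list them explicitly, but the breast health card and the per-patient records should supply them. No visit or procedure changes.

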### Data collection and management

By local research regulations, anonymized data obtained by the CHNs will be initially recorded on paper forms and stored in a secure, locked area to ensure data security and patient privacy. A unique identifier will be assigned to each patient record. These data will be transferred and stored in Research Electronic Data Capture (REDCap) database by trained research assistants who will collect the paper data record from the various centres. The RSAs will be provided with REDCap project server login details, allowing them to securely submit data to the REDCap system. The REDCap server is managed by Obafemi Awolowo University, Ile Ife, Nigeria. All data will be collated from the centres into a central pool. Data on the total number screened at each centre and the number of those with positive findings on CBE/IBE, imaging, and biopsy will be collated every two weeks. Those referred to OAUTHC will be tracked to the final point of care to determine the stage at diagnosis and to obtain information regarding treatment. The principal investigator and research collaborators only will have access to the final study dataset.

### Statistical analyses

All data entered into the REDCap database will be exported as a dataset into R 4.2. Sociodemographic characteristics of the participants will be assessed using medians and interquartile ranges (IQR) for continuous variables and counts and percentages for categorical variables. Participation rate, retention rate, abnormal call rate, rate of late-stage diagnosis, and CDR will be reported as proportions with 95% exact confidence intervals. As for late-stage diagnosis, stage 4 cancers will be considered late-stage. The above-mentioned metrics will be compared between the intervention and control arms using Chi-square tests or Fisher’s exact test. The time intervals from presentation to treatment will be reported using medians and IQR and will be compared between the intervention and control arms using the Wilcoxon rank-sum test. The rate of late-stage diagnosis will be estimated and compared between the intervention and control arms on a yearly basis, starting from baseline, to assess if the intervention arm shows betterment in this rate consistently. Bonferroni correction for type I error will be implemented (α* = 0.0167) for this comparison. A logistic regression analysis which accounts for the ward (random effect) in which the patient was examined will also be performed with late-stage diagnosis as the dependent variable and time of screening, the interaction between the allocated groups (intervention and control arms), and time of screening as the independent variables. For all statistical comparisons (other than the one mentioned immediately above), the type I error rate (α) will be set to 0.05. All statistical analyses will be conducted using R 4.2 software [24]. Sample size calculations were done using the clinfun package of the R 4.2 software [25].

We do not anticipate any missing data due to loss of follow-up because the research team will make every effort to retain recruited participants. However, if missing data issues do arise, we will implement multiple imputation techniques, which impute missing data under the missing at random (MAR) assumption. Sensitivity analysis of the findings after multiple imputations will thereby be performed and these findings will be compared to those obtained from complete case analyses.

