## Introduction

Breast cancer is a major public health challenge in Nigeria with an incidence of 52/100,000 [1], three-fold higher than the incidence four decades ago. Breast cancer incidence is projected to continue to increase in the coming decades. More worrisome, however, is the pattern of presentation–up to 80% of breast cancer cases in Nigeria present in advanced stages [2, 3]. This contributes significantly to high breast cancer mortality rates. This pattern of late presentation has remained unchanged over the last three to four decades [4]. Consequently, when combined with limited access to treatment overall, breast cancer survival in Nigeria is poor compared to high-income countries (HICs) [5–7]. Given the projected rise in breast cancer incidence, there may be an epidemic of advanced breast cancer cases without effective intervention in the coming years [8]. In addition to some recognized biological factors accounting for aggressiveness, it is clear that correctible epidemiological and system-related factors play major roles in late-stage presentation [9]. Both patient and system-related factors contribute significantly to delayed presentation [10]. Delayed presentation and lack of access to diagnostic and treatment facilities are recognized principal factors accounting for poor outcomes in low-middle-income countries (LMICs) [11, 12]. Patient-related factors include lack of breast cancer knowledge, fear of a cancer diagnosis and treatment, use of traditional and alternative remedies, and financial constraints. Awareness creation, community education, and advocacy to address erroneous patient beliefs must therefore form the basis of any early detection program. In addition, a lack of accessible breast cancer screening and the absence of a clearly defined clinical pathway for evaluating women with breast masses, coupled with limited access to diagnostic and treatment facilities, are key system factors requiring intervention [13].

Currently, there are no local data to support a specific breast cancer screening model in Nigeria. Developing a successful breast cancer screening program in a resource-limited setting requires substantial logistical and cultural considerations. Although mammography is recommended as the gold standard based on data from HICs, there are personnel, financial, and infrastructural challenges that limit its applicability for routine use in Nigeria [14].

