We hypothesize that this study will increase breast cancer screening participation rates, facilitate increased uptake of breast evaluation in communities with poor geographical access to standard breast imaging, reduce the incidence of advanced breast cancer cases, and shorten patients’ timelines from presentation to diagnosis and initiation of treatment.

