#### Sample size of cases

The sample size of 4100 study participants anticipated in the intervention arm (Ife North LGA) will include both asymptomatic (40–70 years) and symptomatic (30–70 years) women that will undergo screening and diagnostic evaluations respectively. In any screening exercise, there will be symptomatic cases that will use the opportunity of screening to present for evaluation. We anticipate a CDR of at least 3.5%. This expectation is supported by our previous publication of a mixed screening and diagnostic population in this geographic region demonstrating a breast CDR of 3.5% [19]. The CDR in this study will be the number of cancers detected among all study participants, including both the symptomatic and screening arms.

Our previous data demonstrate that the mean breast tumor size from an entirely symptomatic population at OAUTHC was 10.5 cm. This is much larger than findings from our recent study from the same region which included a screening population which demonstrated an average breast cancer size of 3.3 cm [19, 22]. We therefore project that cancers in the intervention community will be follow a similar pattern.

The primary outcome measure in this study is the stage at diagnosis. To achieve this, we projected the number of cases needed to detect a difference in the proportion of cases based on stage at diagnosis between the two study arms. From our preliminary data of 25 staged cancers, there were 7 (7/12, 58.3%) and 2 (2/13, 15.38%) stage IV cancers in the control and intervention arms respectively, with a 43% difference between the two groups. In order to detect a 43% difference in stage IV diagnoses between the two study arms with 80% statistical power at an alpha of 0.05, 23 cases will be needed in each arm. Our preliminary data show 13 total cancer cases detected in 791 patients and 12 total cancer cases detected in 82 patients in the intervention and control arms, respectively, in the first year. Going by this annual accrual rate, in two years, there should be 26 cancer cases out of 1582 patients in the intervention arm and 24 cancer cases out of 164 patients in the control arm. Therefore, achieving the 23 cases required for statistical significance in the stage at diagnosis in each arm at the end of the 2-year study period is possible.

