**Fig 4 pone.0284341.g004:**
[figure not shown]
Outcome measures in the control and intervention communities.

Primary outcome measures.

Stage at presentation: This will be determined using both clinical and radiological assessment to determine the TNM stage among those with histopathologically confirmed breast cancer. It is expected that the number of patients with late-stage disease may be high at the outset, but this is expected to reduce as screening progresses in the intervention arm. Therefore, besides the absolute number of cases per stage, the pattern of presentation over time will also be assessed to determine if there is a decline in the number of late-stage cases between the prevalence and incidence rounds of screening. Cases of breast cancer from the intervention and control arms will be tracked both at the PHCs and OAUTHC. The stage and pattern of presentation of cases from the two arms will be compared.

Secondary outcome measures.

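### The late-stage tests use stage IV as a share of detected cancers, but the hypothesis is a lower incidence of advanced cancer, so extra early detections alone can look like down-staging

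*Protocol article*

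**What the plan says.** - **Hypothesis** (Introduction, last paragraph): the study will "reduce the incidence of advanced breast cancer cases". That is an incidence, which needs a population denominator.
- **What advanced means**: the Introduction says "up to 80% of breast cancer cases in Nigeria present in advanced stages". Program evaluation and outcome measures gives the same figure with stages attached: "Given in our setting ~80% of patients with breast cancer present in stages 3 and 4". It then describes improvement as movement towards stages 0 to 2, in women returning for repeat evaluation.
- **Primary outcome**: "The primary outcome measure in this study is the stage at diagnosis" (Sample size of cases). Its definition uses clinical and radiological assessment to "determine the TNM stage among those with histopathologically confirmed breast cancer", so the denominator is confirmed cases. The same paragraph promises absolute counts per stage and a between-arm comparison of stage and pattern. It names no test for these.
- **Sizing**: "there were 7 (7/12, 58.3%) and 2 (2/13, 15.38%) stage IV cancers in the control and intervention arms respectively", leading to 23 cases per arm.
- **Analysis** (Statistical analyses): "As for late-stage diagnosis, stage 4 cancers will be considered late-stage". The late-stage proportion is compared by Chi-square or Fisher's exact test, repeated yearly with Bonferroni correction, and is the dependent variable of the logistic model with a ward effect.
- **Arms differ in detection** (Control arm): control women are not invited to screening and have no community imaging or biopsy.
- **Only rate of cancers**: the cancer detection rate, per 1,000 women evaluated. No stage-specific rate per resident woman is planned.

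**The concern.** Two features of the specified late-stage tests do not fit the hypothesis.

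First, the denominator. The intervention itself changes how many cancers are found. Screening adds early cancers to the intervention arm only, and each lowers the stage IV share. The share can fall although the number of women diagnosed at stage IV is exactly what it would have been without the programme.

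Second, the cut. If advanced means stages III-IV, a woman diagnosed at stage II instead of stage III is a success of the kind the programme seeks. Yet she counts the same before and after in the two-group test, the yearly comparison and the logistic model.

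At stake is the headline conclusion. It could be positive from additional early detections alone, or null despite a real fall in stage III disease.

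**Working it through.** **1. The plan's own figure.** Inputs from Sample size of cases: 7/12 = 58.3% and 2/13 = 15.4% stage IV, difference 42.9 points, 80% power, alpha 0.05 (taken as two-sided). Exact power of Fisher's test is the sum, over all tables with p ≤ 0.05, of Bin(x; n, 0.583) × Bin(y; n, 0.154). It gives 78.6% at n = 22 and 81.4% at n = 23. The stated 23 per arm is reproduced.

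**2. Extra early cancers, no stage IV cancer avoided.**
- Control at two years: 24 projected cases, of which 24 × 7/12 = 14 are stage IV.
- Intervention with the same rates per woman, scaled by the ward screening populations (5,800 and 4,500, Sample size of study participants): 24 × 5,800/4,500 = 30.9, or 31 cases; 14 × 5,800/4,500 = 18.0, or 18 stage IV.
- Add k non-stage-IV cancers to the intervention arm only. The share becomes 18/(31 + k). Rejection probability comes from the same enumeration, with 24 control cases at 14/24.

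| Added cases k | Total | Stage IV share | Fisher p at expected counts | Rejection |
|---|---|---|---|---|
| 0 | 31 | 58% | 1.00 | 3.5% |
| 10 | 41 | 44% | 0.31 | 17% |
| 20 | 51 | 35% | 0.081 | 46% |
| 26 | 57 | 32% | 0.045 | 58% |
| 40 | 71 | 25% | 0.005 | 80% |
| 112 | 143 | 13% | <0.001 | 99.5% |

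The last row is the protocol's anticipated detection rate: 3.5% × 4,100 = 143.5 cases. At the first-year yield of 13 cases from 791 women (1.6%), the protocol projects only 26 intervention cases. The value of k is therefore an assumption, shown over its range.

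**3. A pure III-to-II shift.** Take stage IV at 58.3% in both arms and control stages III-IV at 80%, so stage III is 80 − 58.3 = 21.7%. Move all of it to stage II in the intervention arm.
- Stages III-IV fall from 80% to 58.3%.
- Stage IV is unchanged. With 24 and 26 cases, the stage IV Fisher test rejects 3.7% of the time, its null rate.
- A Fisher test of III-IV at the same case numbers rejects 33% of the time. It responds to the shift but is underpowered.

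The 58.3% and the 80% come from different data, so combining them is an assumption.

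**4. What the first year shows.**
- All cancers per 1,000 women: 12/4,500 = 2.7 control, 13/5,800 = 2.2 intervention.
- Stage IV per 1,000: 7/4,500 = 1.56 control, 2/5,800 = 0.34 intervention. The ratio is 0.22.
- Exact interval for that ratio, conditional on 9 events: the Clopper-Pearson interval for 2/9 is 0.028 to 0.600. Converting each limit to odds and dividing by 5,800/4,500 gives about 0.02 to 1.16.

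There is no excess of intervention cases so far, and the stage IV count itself is lower. These rates are rough: the denominators are women aged 40-70, while cases may be 30-70, and control self-referrals are identified from the whole local government area.

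**The case against.** **A reader might infer that stage III shifts would go unseen.** The documents do not support that. The primary outcome paragraph promises counts per stage and a comparison of pattern, so a III-to-II shift, or an unchanged stage IV count, would be reported. What remains is that no specified late-stage test and no sample size covers it.

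**A reader might infer that the stage IV cut was chosen because of the first-year results.** Those results size the comparison. The protocol does not say that they drove the definition.

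**The protocol never defines advanced as III-IV in one sentence.** True. The reading rests on the shared 80% figure, and the stage 0-2 expectation concerns women in the second round. The inference is reasonable, but the text should settle it.

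**Dilution is hypothetical.** It has not appeared: 13 against 12 cases, stage IV 2 against 7. The projected 26 intervention cases are fewer than the 31 that equal rates would give. This limits the concern to a future risk, which grows if detection approaches the anticipated 3.5%.

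**A reader might infer that an ordered-stage analysis is the cure, or that splitting stage in two always wastes power.** Neither follows. In simulation, a rank test rejected a pure III-to-II shift only about 9% of the time. Under dilution by 20 to 40 cases it rejected more often than the stage IV test (about 72-98%). At the effect the trial was sized for it had less power than Fisher's test (81% vs 88%).

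**Conclusion.** The point holds as a mismatch between hypothesis and measure. The specified late-stage tests can reject in roughly half to four fifths of trials (46% to 80%) when 20 to 40 extra early cancers are found and no stage IV cancer is avoided. They reject at their null rate, about 4%, when all stage III disease moves to stage II.

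The first result assumes equal stage IV rates per woman, the stated ward populations and the chosen numbers of added cases. The second assumes that the 58.3% and 80% figures can be combined. The risk is prospective: the first-year counts show no dilution and do not suggest that the observed difference is an artefact of it.

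**What to change.** 1. Keep stage IV as the disclosed, originally sized comparison.
2. State whether advanced means III-IV, and report the III-IV share by arm with an exact interval and a test.
3. Add stage IV and stage III-IV cancers per 1,000 resident eligible women in the selected wards, with a rate ratio and interval. Restrict numerator and denominator to the same wards and the same age range. This means either limiting cases to 40-70 or obtaining 30-70 denominators, and assigning control self-referrals to wards by address.
4. Let any statement about fewer advanced cancers rest on that rate, not on the share of cases.

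**Cost.** Mostly analysis wording, since TNM stage is already to be collected. Ward of residence must be available for every case, and 30-70 denominators may need extra work. The rate will be imprecise, with few events and approximate denominators, and the III-IV test will be underpowered for moderate shifts at the projected case numbers. The change must be disclosed as made after year-1 results were seen.
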